**2.6 Summary and Rationale**

Despite many decades of research and efforts at treatment innovation, at the diagnostic group level people with SSDs continue to experience significant impairments across important outcome domains including personal recovery, physical and mental health related disability, and community functioning. To date, despite the longstanding recognition of heterogeneity in the courses and outcomes for people with SSDs, investigations for the most part have utilized population-based approaches to identify a broad range of demographic, social, environmental, clinical, physical health, and biological predictors of functional outcomes. This approach has relied on the assumption of uniform effects of these predictors across all individuals with SSDs, i.e., that their outcomes and the predictors of these outcomes are homogeneous. Contradictory findings across studies, however, suggest that such effects are not in fact uniform, but rather depend on the population sampled and the underlying trajectories comprising the sampled population. Similar challenges have emerged with regards to inconsistent findings for treatment interventions that have either focused on treating a specific domain of psychopathology as an effector of subsequent improvements in functioning, or broader health and psychosocial interventions that are delivered to individuals based on their diagnosis of an SSD, without precise consideration of individual heterogeneity that may result in similar longitudinal functional disability arising through different underlying mechanisms. Recent data-driven efforts to dissect this heterogeneity have revealed the existence of distinct underlying outcome trajectories among populations of people with SSDs, that are at times indistinguishable based on presenting clinical characteristics but that have very different longitudinal courses. While this has reinforced historic conceptualizations of the distinct course types experienced by people with SSDs, these investigations have focused on narrow measures of functioning, have either been focused primarily on short-term outcomes in the early years of illness or coarsely examined outcomes over longer periods, and have lacked more comprehensive examinations of physical health and biological characteristics that may enhance prediction and delineation of these differential outcome trajectories and the person level.

Priorities regarding what constitutes recovery and relevant functional outcomes in SSDs vary considerably between patients and care providers within a biomedical framework. Traditional objective measures of functioning and recovery from a biomedical perspective typically focus on symptom management and indices of social and role functioning [(Jaaskelainen et al., 2013; Robinson et al., 2004)](https://www.zotero.org/google-docs/?XOUz6z). Patient perspectives, however, typically prioritize areas related to quality of life, self-esteem, connectedness, meaning and purpose, hope and optimism, and empowerment within the construct of personal recovery [(Law & Morrison, 2014; Leamy et al., 2011)](https://www.zotero.org/google-docs/?DC7gQV). There is currently limited research, however, evaluating the longitudinal trajectories of personal recovery and disability in people with SSDs, and how these outcomes interact with each other and with traditional measures of community functioning over time.

In order to advance the understanding of outcome trajectories and potential treatment intervention opportunities to alter these outcomes for individuals with SSDs, there is a need for a broader and more comprehensive evaluation of discrete trajectories of personal recovery, disability, and community functioning. This will advance understanding of their unique and shared longitudinal courses, as well as their underlying clinical, socio-environmental, physical health and biological predictors. No longitudinal study to date, to our knowledge, has examined these concurrent trajectories in individuals with SSDs, nor incorporated physical health, neurobiology, and genetic predictors of these trajectories. The inclusion of EMR-based analytics and provincial administrative health data proposed in this study affords additional unique opportunities for expanded clinical phenotyping and longitudinal outcome evaluations. The proposed study also sets the stage for the co-design and testing of real-world interventions targeting discrete outcome trajectory subtypes through a precision medicine approach in order to improve the individual’s outcome trajectory and promote recovery and reduce the enduring disability they experience.

**3.0 METHODOLOGICAL DETAILS**

This study will utilize a longitudinal sequential cohort design, with broad sampling across age ranges and phases of illness for individuals with SSDs. The characterization and prediction of trajectories of functional disability will provide the foundation for integration of interventions targeting specific predictors of functional disability that will be co-designed with patients, family members, and service providers, and evaluated as embedded trials within this cohort study. Selection of outcomes measures and assessments including the comprehensive measurement of relevant domains of functional outcome and recovery, was informed by guidance from patient and family member representatives of the study steering committee, their integration within routine clinical services at CAMH, and their alignment with other large clinical research initiatives currently taking place both locally and internationally. Study assessments will be completed at baseline, and longitudinal as outlined in Appendix 1. Extended follow-up beyond the initial three years will be pursued through external funding to support this work.

**3.1 Participants**

Participants will be eligible for this study if they: 1) are 16 years of age and older; 2) have a DSM-5 diagnosis of any schizophrenia spectrum disorder (SSD; e.g., schizophrenia, schizoaffective disorder, schizophreniform disorder, brief psychotic disorder, delusional disorder, unspecified schizophrenia spectrum or other psychotic disorder, other specified schizophrenia spectrum and other psychotic disorder, substance/medication-induced psychotic disorder), or related psychotic disorders (including bipolar I disorder with psychotic features or major depressive disorder with psychotic features); and 3) have adequate fluency in English to participate in clinical care without the need for a translator . Of note, participants will be eligible regardless of duration of illness, co-morbid mental or physical health conditions, capacity to consent to treatment, or whether they are receiving inpatient or outpatient services at CAMH. Participants will provide written informed consent, and for those individuals deemed incapable to consent to treatment by their treatment team and have a substitute decision-maker (SDM), their SDM will provide written informed consent in conjunction with participant assent to study participation. These broad eligibility criteria will serve to support generalizability of the sample and maximize the opportunity to evaluate the influence of common co-occurring illnesses on longitudinal outcome trajectories. Caregivers of study participants will also be invited to participate with the consent of the study participant.

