**1.1 Objectives and Hypotheses**

**Objective 1:** Determine the longitudinal functional trajectories of individuals with SSDs across three co-primary domains consisting of personal recovery, disability, and community functioning.

**Hypothesis 1a:** Within each outcome domain, we anticipate approximately 4-5 longitudinal trajectories, consisting of early-sustained improvement, delayed gradual improvement, early improvement / delayed mild-moderate deterioration, early improvement / delayed moderate-severe deterioration, and persistent disability.

**Hypothesis 1b:** We hypothesize that early improvement in personal recovery trajectories will be antecedents of subsequent improvement in disability and community functioning trajectories, while deteriorating or persistent disability, particularly with regards to physical disability, will be early antecedents of worse community functioning.

**Objective 2:** Develop and test predictive models to accurately determine functional trajectories at the person level.

**Hypothesis 2a:** Trajectories of functioning will be differentiable based on sociodemographic and treatment factors, psychopathology, physical health, and biological measures.

**Hypothesis 2b:** A subset of these differential baseline sociodemographic, symptoms, and biological measures will enable the prediction of individual functional trajectories with high positive predictive power.

**Objective 3:** Based on the predictors of longitudinal outcome trajectory subtypes, co-design and pilot targeted real-world interventions developed with patients, family members, and service providers.

**Hypothesis 3:** The co-designed interventions targeting the individual’s longitudinal outcome trajectory will be feasible to implement, satisfactory to participants, and offer preliminary evidence of efficacy for improving longitudinal outcomes compared to treatment as usual.

**Exploratory Objective:** Develop and validate a novel automated method using natural language processing (NLP) and machine learning (ML) to interrogate electronic medical records for the ascertainment of retrospective temporal trajectories in symptom, physical health, treatment, and functional outcomes.

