Longer-term longitudinal studies have served to confirm these early outcome trajectories. In a three-year follow-up study of individuals after a first episode of psychosis, [Chang et al., (2018)](https://www.zotero.org/google-docs/?omLmB7) identified four outcome trajectories based on the SOFAS, comprising early improvement, gradual improvement, early improvement with later deterioration, and persistently poor outcome subtypes. Individuals across these four trajectories were differentiable based on a higher preponderance of females among better outcome trajectories, higher education attainment in the better outcome trajectories, and a lower frequency of hospitalization at first hospitalization among those demonstrating early improvement. Psychopathology was not predictive of functional outcome trajectories with only a trend related to the severity of negative symptoms at baseline. Finally, data from the Suffolk County Mental Health Project has been used to evaluate 20-year trajectories of social functioning for individuals with SSDs following their first admission, albeit more coarse-grained due to large gaps of 6 and 10 years between assessments in the later stages of follow-up. Initial comparisons of longitudinal functioning for individuals with SSDs compared to those with mood disorders with psychosis and other psychotic disorders described a substantial and consistent decline in functioning over time for people with SSDs, although with notable heterogeneity in levels of functioning between individuals in the same diagnostic group [(Kotov et al., 2017)](https://www.zotero.org/google-docs/?k8L8Mg). Subsequent data-driven examination of social functioning trajectories across these disorders revealed four trajectory subtypes consisting of preserved, moderately impaired, severely impaired, and profoundly impaired functioning [(Velthorst et al., 2017)](https://www.zotero.org/google-docs/?AZq3mv). These trajectories were differentiable even early on based on premorbid adjustment prior to illness onset, sociodemographic characteristics including male sex and ethnicity, and over the course of follow-up assessments differed in the severity of negative symptoms and antipsychotic use, and to a lesser extent severity of positive symptoms.

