**3.9.1 Study population and design**

Participants who consent to have their data linked with administrative health data will be eligible to have both historical and future services use linked from the time of cohort entry. Participants who have a OHIP card will be able to consent for direct linkage, and participants who consent but have any uncertainty with their OHIP number will be linked using a deterministic process.

Further use of administrative data will enable comparison of service use and outcome between:

1. Participants that are part of the cohort at CAMH (accessing specialized mental health services at CAMH),
2. People with a SSD who are accessing specialized mental health services in the community (including ACT, ICM and case management services but not at CAMH), and
3. People with a SSD who reside in Toronto but are not currently receiving specialized mental health services

Diagnosis of a SSD in the comparison groups in the health administrative data will be ascertained using a validated algorithm that captures all incident cases of SSD [(Kurdyak et al., 2015)](https://www.zotero.org/google-docs/?SkNgwy). The comparison groups will be restricted to people who reside in areas of Toronto where outpatient services at CAMH are offered and restricted to people who have not received regular outpatient services at CAMH.

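### Affective psychoses are eligible although Objective 1 and the design concern SSDs, and the ICES comparison defines its cohort group and its comparators by different case rules

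*Protocol*

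**What the plan says.** **Target population.** Objective 1 (Section 1.1) is to "Determine the longitudinal functional trajectories of individuals with SSDs across three co-primary domains". Section 3.0 describes a cohort design "with broad sampling across age ranges and phases of illness for individuals with SSDs". The first power target in Section 5.0 is likewise the trajectories of people with SSDs. Objective 2, "Develop and test predictive models to accurately determine functional trajectories at the person level", names no diagnosis and takes over the trajectories found under Objective 1.

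**Eligibility.** Section 3.1 lists the SSDs and then adds, as a separate category, "or related psychotic disorders (including bipolar I disorder with psychotic features or major depressive disorder with psychotic features"). It also says that "participants will be eligible regardless of duration of illness". The stated reason for the breadth is that "These broad eligibility criteria will serve to support generalizability of the sample". No cap or expected share is given for the affective psychoses.

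**Analysis.** Section 5.0 fits growth mixture models to each co-primary outcome in the whole sample. It singles out age range and illness stage as the heterogeneity to deal with.

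**ICES comparison.** In Section 3.9.1, group 1 is the cohort members who are linked, without a diagnostic restriction. Groups 2 and 3 are people with an SSD, in specialised community services and in no specialised service respectively. Their diagnosis "in the comparison groups in the health administrative data will be ascertained using a validated algorithm that captures all incident cases of SSD". Section 3.9.2 matches 1:1:1 on a propensity score without replacement, and Section 3.9.5 lists diagnosis among the covariates.

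**The concern.** Two different things follow from the wider eligibility.

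In the ICES comparison, exposure is the type of service received, and the primary outcome is the number of mental health hospitalisations after cohort entry. A cohort member with bipolar I or major depression with psychotic features belongs to group 1. As Section 3.9.1 is worded, no one with only that diagnosis can belong to group 2 or 3. Illness duration has the same asymmetry: any duration in the cohort, against an algorithm described in terms of incident cases. A difference in hospitalisations or costs could then come from who counts as a case and not from the service.

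In Objectives 1 and 2, the trajectories are to be reported as those of people with SSDs but are estimated in a wider group. If course differs by diagnosis, class sizes and shapes would partly reflect the diagnostic mix.

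**Working it through.** **1. The plan's own figures.** With 1000 enrolled, 25% attrition and a smallest class of 15%: 1000 × 0.75 × 0.15 = 112.5, stated as 112 in Section 5.0. This reproduces. There is no arithmetic error; the question is which population the 1000 represent.

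**2. ICES case rules side by side.**

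| | Group 1 | Groups 2 and 3 |
|---|---|---|
| Source of diagnosis | DSM-5 eligibility, SCID-5 at baseline | Administrative algorithm |
| Diagnoses | SSD or affective psychosis | SSD |
| Duration | Any | Algorithm described as capturing incident cases |

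A propensity score balances a covariate only where its values occur in all groups. If the affective share in group 1 is s and the share in the comparators is 0, the standardised difference in diagnosis is s / √(s(1−s)/2) = √(2s/(1−s)). The share s is not in the documents, so a range is assumed:

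- s = 5%: √(0.10/0.95) = 0.32
- s = 10%: √(0.20/0.90) = 0.47
- s = 20%: √(0.40/0.80) = 0.71

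These values also assume that the algorithm picks up no affective psychosis. If it picks up some, the difference is smaller.

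**3. Size of the affective group in the trajectory models.** Affective completers number 750 × s: 75 at 10%, 112.5 at 15% and 150 at 20%. At an assumed 15% the group equals the smallest planned class. This shows only that it would be large enough to matter, not that it forms a class.

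**4. Would classes reproduce diagnosis?** As an illustration, let the affective group differ from SSD by a constant D standard deviations over the 7 visits, with intraclass correlation r. The variance of a person's mean is r + (1−r)/7, and the AUC for telling diagnosis from the whole profile is Φ(D / √(2(r + (1−r)/7))).

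- D = 0.3, r = 0.7: AUC 0.60
- D = 1.0, r = 0.5: AUC 0.83

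D and r are assumptions. Over this range, diagnosis and class could be associated but would be far from identical.

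**5. Price of an SSD-only primary set.** The calculation assumes a 25% class, a binary predictor with prevalence 0.30 in the other classes, and an odds ratio of 1.68. The prevalence in the class is then 0.72/1.72 = 0.419. A two-sided 5% two-proportion test gives:

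| s | SSD completers | Smallest 15% class | Power for OR 1.68 |
|---|---|---|---|
| 0 | 750 | 112 | 0.84 (stated 0.82 to 0.85) |
| 10% | 675 | 101 | 0.80 |
| 20% | 600 | 90 | 0.76 |

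The simulated power for class enumeration (0.80, or 0.68 with uneven classes) cannot be recomputed because its inputs are not given.

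**The case against.** The breadth is deliberate and justified in Section 3.1, and Section 2.6 criticises treating outcomes as uniform within a diagnosis. Section 2.4 does report that comparisons of SSDs with psychotic mood disorders and other psychoses "described a substantial and consistent decline in functioning over time for people with SSDs". It also notes wide variation within diagnostic groups, and then cites four trajectory subtypes found across these disorders together. Pooling therefore has a precedent in the protocol itself. Recruitment runs largely through the Schizophrenia Division, so the affective share may be small. SCID-5 is done for everyone, so diagnosis by class can be tabulated at any time. All of this stands, and it argues against making SSD-only the primary set for Objectives 1 and 2.

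For ICES, diagnosis is a matching covariate and Section 3.9.6 promises a balance check. A check would reveal an imbalance but could not repair one that the group definitions create. It is fair that the protocol does not say whether the algorithm in practice also captures affective psychosis. The title of the cited validation study speaks of chronic psychotic illness, so the contrast between incident cases and any duration rests on one word in Section 3.9.1.

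A reader might infer that the trajectory classes will simply recover diagnosis, or that every objective is stated for SSDs. Neither is supported. The first is conjecture (step 4 of the working), and in Section 1.1 only Objective 1 names SSDs.

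**Conclusion.** The concern holds in two limited respects.

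- **ICES groups.** As written, the three groups do not share a case definition, so the service contrast is mixed with case definition, and matching on diagnosis cannot remove this for diagnoses that the comparators exclude. The extent depends on two unknowns: the affective share, and what the algorithm captures. At assumed shares of 5% to 20% and no capture, the standardised difference in diagnosis is 0.32 to 0.71.
- **Population wording.** Objective 1, the design statement and the eligibility criteria describe different populations. Trajectory classes may be confounded with diagnosis, to an unknown degree. The supplementary analysis suggested for this is an inexpensive addition; the protocol is not defective for leaving it out.

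**What to change.** **ICES comparison (Sections 3.9.1 and 3.9.2).** Apply the administrative algorithm to linked cohort members as well, and restrict the matched analysis to those who meet it, so that all three groups share one case definition. State whether the algorithm captures affective psychosis, and whether it is meant to select incident cases only. The cost is one derived flag and a smaller matched sample. The loss is roughly the affective share (if the algorithm excludes those diagnoses) plus any SSD participants whom the algorithm misses.

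**Objectives 1 and 2 (Sections 1.1, 3.0, 3.1 and 5.0).** Keep the model on all participants as planned. Reconcile the population wording, for instance by stating Objective 1 for SSDs and related psychotic disorders. Add a supplementary class enumeration restricted to SCID-5-confirmed SSD, and report diagnosis by class. The cost is wording and one further model run per outcome on data already collected. The primary sample size and power are unchanged, though the supplementary run will be less powerful, as step 5 of the working shows.

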**3.2 Procedures**

Recruitment and Informed Consent:

At the initial baseline visit, participants and their SDM where applicable, will be provided detailed study information via the informed consent form, and through discussion with the study team. The informed consent process will take place in person or through Cisco Webex video conferencing and REDCap as described in CAMH SOP #HSR 229: e-Consent Framework. Study staff will assess eligibility via the inclusion/exclusion criteria following obtaining consent. No study procedures will be completed prior to obtaining informed consent.

Participants will be recruited through the Schizophrenia Division Central Recruitment Model (REB #036/2020), the CAMH Research Registry, physician/clinician referrals, and through direct contact with former research participants who participated in previous studies of the Principal Investigators and Co-Investigators of this study who consented to be contacted for future research studies. If a patient is interested to learn more about the study, the physician/clinician may pass the patient’s preferred contact information to a research staff for follow up. A study recruitment flyer will be shared with participants who need more information about the study. This flyer will also be posted on bulletin boards across CAMH. Study information will also be available to participants through the CAMH Research Connect website.

The Schizophrenia Division Centralized Recruitment Procedure will be used to recruit participants for this study. The Centralized Research Personnel will prescreen patients for eligibility to participate using minimal inclusion/exclusion criteria outlined in REB #036/2020. Once a patient has been identified, the Centralized Research Personnel will send preferred contact information to the Study Specific Research personnel who will reach out to the patient to further explain the study. No information will be passed to the Study Specific Research Personnel prior to the patient’s verbal consent.

For e-Consent, participants will be provided with a read-only copy of the informed consent form via REDCap prior to conducting the consent discussion. The link may be used by participants as many times as they wish (it is not single-use). Upon clicking the link, participants or their caregiver/substitute-decision maker will review the landing page, and continue on to the informed consent form text. The entire contents of the informed consent form will be displayed according to the current REB approved consent form, minus the signature/attestation page(s). Informed consent will be documented using the REDCap e-Consent Framework. Following the consent discussion, the prospective participant or their caregiver will be sent a link to the e-consent via email or the chat feature in WebEx. The participant will complete the e-consent and be provided with the option to download and/or email themselves the signed informed consent form. If email is chosen, the email will only be used for this purpose (it is not retained by REDCap). Following the participant and/or caregiver signature, the person conducting the consent discussion will complete the Person Conducting Consent Discussion Attestation Page. PDF copies of the signed informed consent forms and Attestation pages will be retained in the REDCap File Repository. The research team will provide the participant and/or their caregiver with a copy of the fully signed informed consent form via mail and/or email, in accordance with the participant’s wishes. When the informed consent process takes place in person, participants and/or their caregivers will be provided a copy of the fully signed informed consent form in person at the time of consent. As consent is an ongoing process, even after a participant has provided initial consent to participate, we will use subsequent visits and the implementation of study procedures and assessments as opportunities to again explain what is being done and to ensure continued informed consent.

Study Procedures:

Following written informed consent, enrolled participants will undergo comprehensive clinical and functional characterization using a series of standard measures, including structured diagnostic assessment, clinical assessments to index severity of psychiatric symptoms, substance use, physical health, cognition and functioning, collection of treatment and medical history data from participants and their electronic medical record, as well as laboratory, genetic, and imaging assessments (described in detail in Sections 3.3 - 3.7). This will be complemented by characterization of social and health equity factors and linkage with broader provincial health system data held at the Institute for Clinical Evaluative Sciences (ICES). Study visits will take place at baseline and every 6 months over a period of 3 years as outlined in Appendix 1. Participant assessments will be conducted either in-person or virtually, where possible, based on participant preference.

Study Withdrawal/Termination:

Reasons for withdrawing individual participants from the study may include one or more of the following: a) major protocol violation b) participant lost to follow-up c) withdrawal of consent.

Any participant may be discontinued from the study at the discretion of the investigators if this is deemed to be in the best interest of the participant. The decision may be made either to protect the participant’s health and safety, or because it is part of the research plan that people who develop certain conditions may not continue to participate.

If a participant initially consents to participate and later chooses to withdraw from the study, they will be offered the opportunity to withdraw data and/or samples that have not yet been anonymized, published, or disseminated.

